# Double-chamber syringe versus classic syringes for peripheral intravenous drug administration and catheter flushing: a study protocol for a randomised controlled trial

**DOI:** 10.1186/s13063-019-3887-1

**Published:** 2020-01-14

**Keywords:** Double-chamber syringe, Clinical research, Effectiveness, Safety

## Abstract

**Background:**

The prevention of catheter-related complications is nowadays an important topic of research. Flushing catheters is considered an important clinical procedure in preventing malfunction and several complications such as phlebitis or infection. Considering the latest guidelines of the Infusion Nurses Society, the flushing should be carried out both pre- and post-drug administration, requiring different syringes (with associated overall increased times of preparation/administration of intravenous medication by nurses, and also increasing the need for manipulation of the venous catheter).

**Methods/design:**

A multi-centre, two-arm randomised controlled trial with partially blinded outcome assessment of 146 adult patients. After eligibility analysis and informed consent, participants will receive usual intravenous administration drugs with flushing procedures, with a double-chamber syringe (arm A) or with classic syringes (arm B). The outcomes assessment will be performed on a daily basis by an unblinded ward team, with the same procedures in both groups. Some main outcomes, such as phlebitis and infiltration, will also be evaluated by nurses from a blinded research team and registered once a day.

**Discussion:**

The study outlined in this protocol will provide valuable insight regarding the effectiveness and safety of this new medical device. The development of this medical device (dual-chamber syringe, for drug and flush solution) seems to be an important step to facilitate nurses’ adoption of good clinical practices in intravenous procedures, reducing catheter manipulations.

**Trial registration:**

ClinicalTrials.gov, NCT04046770. Registered 13 August 2019.

## Background

The insertion of a peripheral intravenous catheter (PIVC) is the most frequent invasive procedure performed in nursing clinical practice. These invasive devices are inserted into patients’ peripheral veins and enable the intravenous administration of fluids, blood products, and drugs directly into the bloodstream [1, 2]. However, a wide range of complications can occur, such as mechanically induced complications (partial dislodgement or accidental removal, infiltration, extravasation, occlusion) [3–13], those of an infectious nature (bacterial or fungal sepsis) [7, 8, 10, 12, 14], or phlebitis [3–5, 15].

Phlebitis (irritation or inflammation of the vein wall, associated with warmth, tenderness, erythema, or palpable cord) is the most frequent PIVC-related complication, which may have mechanical, chemical, or bacterial causes [5, 13]. Thus, assessment of the PIVC insertion site must be performed daily and use of a transparent sterile dressing for stabilizing and protecting the catheter [16] is essential to allow for visual inspection of the catheter site. Transparent sterile dressings require less frequent changes than do standard gauze and tape dressings [17–19], and have also been associated with fewer accidental PIVC removals [20]. The main repercussion of phlebitis is pain, resulting in the need for new catheterization and momentary interruption of the prescribed intravenous therapy. Moreover, extravasation or infiltration of fluids may be responsible for local oedema due to the pervasion of intravenous fluid into the interstitial compartment, causing inflammation of the tissue around the catheter site. Occlusion is defined as any circumstance in which the PIVC is not able to be flushed or infuse fluids/medications and it is a clinical sign of catheter malfunction [21].

The use of a PIVC has also been associated with the risk of nosocomial bacteraemia [22], resulting in significant rates of patient morbidity and mortality [23, 24]. The European Centre for Diseases Control and Prevention (ECDC) indicates a higher infection prevalence in Portugal (10.6%) compared with the European mean prevalence (5.7%) [25]. In fact, the last report of the Program for Prevention and Control of Infection and Resistance to Antimicrobials (PPCIRA) for 2018 states an infection prevalence of 7.8% for acute hospitals in Portugal, one of the highest in Europe [26]. The prevention of catheter-related complications usually relies on precautions during catheter insertion (e.g. hand hygiene, use of the aseptic non-touch technique, catheter size, anatomical insertion site, dressings) and catheter surveillance (e.g. maintenance time, flushing, medications) and the overall competence and qualifications of the nurses [16–19, 27].

Flushing the catheters with 0.9% sodium chloride is the most important factor in preventing malfunction by maintaining catheter patency. International standards of care recommend the flush volume to be at least equal to twice the internal volume of the catheter system (catheter, extension set, and/or needleless injection system) [17]. In fact, professionals’ flushing practices appear to vary widely with regard to solutions, frequency, volumes, and techniques [13, 21, 28, 29]. PIVCs should be flushed at the time of medication administration [17, 30]. The flushing practice usually implies the initial aspiration of blood to ascertain vascular access device patency and minimum pre- and post-drug administration flushes using a pulsatile technique [17]. This has proved to be a simple, effective, and inexpensive technique to reduce catheter bacterial colonization [31]. The theoretical purpose of flushing is to maintain catheter patency by preventing internal luminal occlusion, reducing build-up of blood or other products on the device’s internal surface, and preventing interactions between fluids or drugs [32–36]. This procedure is also believed to prevent some important complications such as line blockages by blood clots or air bubbles/occlusion, phlebitis, and infection [37].

Traditionally, this process has been done using two or more syringes to assess patency (pre-flushing), drug delivery, and final flush solution. This process is time-consuming for nurses (both in the preparation and administration of the intravenous therapeutics), requires more manipulations of the venous access, and involves higher economic costs. Commercially prepared prefilled flush syringes are useful in reducing preparation and administration times as well as promote adherence to some of the recommended clinical practices, such as the aseptic non-touch technique and intravenous flushing practice [29]. Despite this, they do not address the need to reduce the number of catheter manipulations as well as the associated economic costs (using pre-filled syringes still dictates that the professional needs two or more syringes to accomplish the intravenous therapeutic process).

Double-chamber syringes have been developed as a drug and device combination product that enables the reconstitution and administration of drugs in fixed doses. Some of the existing syringes marketed for the administration of multiple fluids have not been well-received because they generally require the delivery of two fluids, one prefilled flush solution and an empty chamber to be filled with the medication. However, no syringe has become widely accepted that allows filling both chambers of a single syringe in place, one for routine medication administration and the other for subsequent catheter flushing. To address this gap in the market, a double-chamber syringe was developed that enables the filling and administration of drug and flush solution. The clinical effectiveness and safety parameters of this double-chamber syringe need to be determined.

## Methods/design

### Objectives

The main objective is to establish the clinical effectiveness and safety parameters of the new medical device: a double-chamber syringe for intravenous administration and flushing. In order to accomplish this objective, the main outcomes measured are related to PIVC complications, namely vascular trauma (phlebitis and infiltration) and occlusion. The secondary outcomes are related to the catheters (such as other removal causes, maintenance time, insertion attempts, and the number of catheters needed to achieve the prescribed intravenous treatment), but also explore patient’s satisfaction of the intravenous treatment received, as well as nurse’s satisfaction with the medical device (including the perception of safety/risk).

### Design and study setting

The study protocol was developed under the SPIRIT 2013 Guidelines [38]. The SPIRIT checklist is provided as Additional file 1. This is a multi-centre (three hospitals), two-arms, partially blinded randomised controlled trial (RCT; Fig. 1).

**Fig. 1 Fig1:**
[figure not shown]
Flow diagram of the parallel randomised controlled trial with two groups (CONSORT 2010)

The principal investigator will obtain initial agreement from the three hospitals involved, and a lead investigator in each centre will be nominated, becoming the local contact person during the study. Before the clinical study starts, an investigator meeting will be conducted in each centre in order to present the clinical protocol and trial-specific procedures to the nurses’ research teams. The clinical study is planned to last 9 months from the start of the recruitment process to the reporting of results.

### Participant recruitment and eligibility criteria

The participants will be recruited in the orthopaedic departments of the three hospitals where the clinical study will take place. Prior to baseline data collection, eligible participants will be recruited by a research assistant nurse at the time of admission. Therefore, no plans will be made to increase the recruitment of participants across other clinical settings. Patients are admitted if they meet the following inclusion criteria:
Patients aged 18 years or above, admitted to the orthopaedic departmentPatients with the ability to fully communicate in PortuguesePatients able to consentPrescribed PIVC for intravenous therapeutic administrationPIVC expected to remain for at least 24 hPIVC inserted at the orthopaedic departmentPIVC size 18G or 20GAnatomical insertion site in arm, forearm, or back of the handPIVC secured with a transparent, semi-permeable polyurethane film dressing

Patients will be excluded if they meet any of the following exclusion criteria:
Patients with a known infectious diseasePatients with leucocytosis, defined as ≥ 1200 leukocytes/mm^3^ [39]Patients with anaemia, with haemoglobin levels < 13 g/dl for men and < 12 g/dl for women [40]Patients receiving immunosuppressive treatment within 6 months prior to hospital admissionPatients receiving chemotherapy or radiotherapy within 6 months prior to hospital admissionPatients with body mass index below 16 kg/m^2^ or above 39 kg/m^2^ [22]Anatomical insertion site in flexion areas (e.g. cubital fossa region) or lower membersSkin lesions at the insertion site (e.g. previous infiltration, dermatitis, burns) and skin alterations such as tattoosPeripheral venous alterations resulting from previous hospital admissions

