### Sample size

Commonly, the sample size calculation is based on an expected incidence of the primary outcome. In our study, we have several primary outcomes regarding PIVC-related complications. Therefore, the sample size was calculated considering the lower prevalence value in Portuguese contexts for one of the primary outcomes (namely occlusion, with a 19% prevalence rate) [13, 28]. Also, the sample size determination was established using G*Power software, taking into consideration the type I (α) error level, the statistical power (type II error, β), and the standard deviation of the measurement for continuous outcomes. Fisher’s exact test comparing the proportions in two groups (*p* control = 0.19; *p* experimental = 0.05) are considered (Table 2). Ensuring a type I error of 5% and a statistical power of 80%, the estimated sample size is 146 participants (73 participants in each group).

**Table 2 Tab2:** Sample size estimation

Input		Output	
Tail(s)	One	Sample size group 1	73
Proportion p1	0.19	Sample size group 2	73
Proportion p2	0.05	Total sample size	146
α err prob	0.05	Actual α	0.0197
Power (1-β err prob)	0.80		
Allocation ratio N2/N1	1		

Fisher’s exact test: Proportions, inequality, two independent groups

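### The leucocytosis exclusion is defined by a count far below ordinary adult values, so as printed it would exclude nearly every eligible patient

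*Protocol article*

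**What the plan says.** In the protocol article, under Participant recruitment and eligibility criteria, one exclusion names patients with leucocytosis and then defines the term numerically, with a greater-than-or-equal sign, as "1200 leukocytes/mm^3^ [39"]. The list is introduced by "Patients will be excluded if they meet any of the following exclusion criteria", so meeting this one line is enough to exclude a patient. No other section gives a different white-cell threshold, another unit or a correction.

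The recruitment target is set under Sample size: "the estimated sample size is 146 participants (73 participants in each group"). The section on eligibility says that recruitment will not be widened to other clinical settings. The section on randomisation places two eligibility screenings before allocation.

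**The concern.** The clinical term and the figure attached to it point in opposite directions. The term describes a high count. The figure is one that nearly every adult exceeds. Because the article presents the figure as the definition, a screener who follows the number and a screener who follows the word reach opposite decisions on almost every patient.

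Two outcomes are possible, and they are alternatives. If the number is applied, recruitment in the three orthopaedic departments effectively stops, and the article offers no other setting to draw on. If staff see the conflict and use a cut-off of their own, the trial recruits, but the eligibility rule is then unwritten and may differ between hospitals. The Discussion relies on strict eligibility criteria to control variables that could affect the results. This criterion cannot do that as printed.

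**Working it through.** **Inputs**

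- Threshold: exclude if the count is ≥ 1200/mm³ (article, eligibility criteria).
- Rule: any single criterion excludes (same section).
- Target: 146 participants, 73 per group (article, Sample size).
- Adult reference range: not given in the article. Assumed at about 4000–11000/mm³ and varied from 3000–9000 to 4500–11000/mm³.

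**The plan's own figures.** The threshold is stated, not derived, so there is no calculation to reproduce. The nearby derived figure is the sample size. The article sets it by "Fisher’s exact test comparing the proportions in two groups", with 0.19 against 0.05, one-sided, and "Ensuring a type I error of 5% and a statistical power of 80"%. Exact enumeration of the one-sided Fisher test gives power 0.7944 at 72 per group and 0.8003 at 73 per group. The actual type I error at a common rate of 0.05 is 0.0197. Both agree with Table 2, and the white-cell threshold does not enter this calculation.

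**Share of patients who escape the exclusion.** Treat each assumed range (L, U) as a central 95% interval of a normal distribution:

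- mean = (L + U)/2
- SD = (U − L)/3.92
- z = (1200 − mean)/SD
- share below 1200 = Φ(z)
- patients needed = 146/Φ(z)

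| Assumed range (/mm³) | Mean | SD | z | Share below 1200 | Otherwise eligible patients needed for 146 |
|---|---|---|---|---|---|
| 3000–9000 | 6000 | 1531 | −3.14 | 0.086% | about 170,000 |
| 3500–10500 | 7000 | 1786 | −3.25 | 0.058% | about 251,000 |
| 4000–11000 | 7500 | 1786 | −3.53 | 0.021% | about 697,000 |
| 4500–11000 | 7750 | 1658 | −3.95 | 0.004% | about 3.7 million |

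The share excluded is therefore at least 100% − 0.086% = 99.91%. A log-normal shape makes the share below 1200 smaller still: at most about 8.5 × 10⁻⁸, for the 3000–9000 range.

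These are far-tail values under an assumed shape, so only their order of magnitude should be read. The conclusion does not depend on the choice of range: even the lowest assumed lower limit, 3000/mm³, is 2.5 times the threshold (3000/1200).

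**The case against.** The strongest reply is that this is a plain slip which nobody would apply. The criterion opens with the clinical term, and hospital staff would notice the conflict at the first ordinary blood count. The article is also not the full protocol. It refers to a protocol version 5, to investigator meetings at each centre, and to case report forms and templates still to be reviewed by ethics committees. The wrong figure may appear only in the article.

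Much of this stands. An empty eligible pool follows from the literal rule and is not a forecast of what the trial would do. But recognising a slip does not correct it: the article does not show whether the digits or the unit are wrong, and sites that guess may guess differently.

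Several stronger readings are tempting, and the article does not support them:

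- A reader might infer that the figure will be carried onto screening forms and into the registry entry. Neither is shown.
- A reader might infer that every enrolled patient would be a protocol deviation. That requires the operative protocol to hold the same number, no correction to be issued, and sites to substitute their own value silently. The article establishes none of these.
- A reader might infer that the immunosuppression and chemotherapy/radiotherapy exclusions would remove most patients with very low counts. Those exclusions concern treatment in the previous 6 months, not counts, and the article gives no figure.
- A reader might infer that a digit was dropped and restore it. Reference 39 is not at hand, so the intended value cannot be established from the article.

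**Conclusion.** The concern holds as an error in an operative eligibility threshold. The printed number contradicts the term it defines, and nothing else in the article corrects it. Applied literally, it would exclude at least about 99.9% of otherwise eligible patients, admit only those with severely low counts, and put 146 participants out of reach. The size rests on an assumed adult reference range between 3000–9000 and 4500–11000/mm³; the direction holds across that whole span.

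The effect is on who can be enrolled and on whether the three hospitals apply the same rule. It does not reach the sample size calculation. Nor does it by itself bias one arm against the other, because eligibility is settled before allocation. It should be put right before screening begins, since the criterion cannot be used as written.

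**What to change.** Before the first patient is screened:

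1. Reconcile the number and the unit in the leucocytosis criterion with the word itself and with the definition in reference 39.
2. Have the sponsor's clinicians confirm the reconciled criterion. No replacement value is proposed here.
3. Check that the full protocol and the screening documents carry the same corrected figure, and issue a correction to the article.

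The cost is small. It is a correction to one criterion plus a check of the related documents. According to Trial status, the protocol had still to be submitted to the Portuguese authorities and first recruitment was expected by July 2020. The ethics section adds that recruitment at the hospitals waits for local approval. After enrolment has begun, the same correction would need an amendment and a review of the eligibility of those already randomised.

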### Randomization, concealment, and group allocation procedures

The participants will be randomised after meeting two eligibility criteria screenings (Table1). Eligible and consenting participants will be randomly assigned to one of two treatment groups (arm A, double-chamber syringe; arm B, traditional syringes) using simple randomization with a 1:1 ratio. In each participating hospital ward nurses will have access to a central randomization and online registration system (https://www.sealedenvelope.com/). Before patient inclusion in the study, ward nurses will log into the online system and provide the participant’s anonymous ID number. The central system will randomly allocate the participant to one of the two groups and inform the nurse in real time. All allocations will be recorded into the central system and can only be accessed by the study’s principal investigator, ensuring allocation concealment across sites.

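### Simple randomisation is fixed for 146 patients in three hospitals with no pre-specified hospital adjustment; hospital-stratified blocks with a matching analysis would be a cheap, modest improvement

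*Protocol article*

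**What the plan says.** Design and study setting describes a "multi-centre (three hospitals), two-arms, partially blinded randomised controlled trial". The section on randomisation, concealment and group allocation assigns patients "using simple randomization with a 1:1 ratio" and states that "ward nurses will have access to a central randomization and online registration system", with each allocation returned in real time. It mentions no blocking, stratification or minimisation. Sample size plans for "73 participants in each group".

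Data collection, management, and analysis lists the t-test, Mann-Whitney, χ² and Fisher's exact tests, none with a hospital term. It also says that baseline variables differing significantly between the arms will be controlled for in the outcome analyses, and that no additional analyses will be done. Hospital is not named in that rule.

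**The concern.** Coin-toss allocation leaves the balance of arms within each hospital to chance. Each hospital has its own ward team, and occlusion, the outcome that sets the sample size, is rated only by unblinded ward nurses. Hospital is therefore a plausible prognostic factor, although the article gives no hospital-level figures.

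With few expected events, a lopsided hospital adds noise to the comparison and invites questions about the result. The infrastructure that would prevent this is already planned. What is at stake is some precision, visible balance by hospital, and an adjustment fixed in advance. The validity of the test is not at stake.

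**Working it through.** **Inputs from the protocol article.** N = 146, three hospitals, simple 1:1 allocation; occlusion 0.19 (control) against 0.05 (experimental); one-sided Fisher's exact test at 5% with 80% power (Table 2).

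**Assumed, because the article does not give them.** Hospital sizes 49/49/48 or 80/40/26; hospital occlusion rates 10/19/28% or 5/19/33%.

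**1. The plan's own figure.** Enumerating both binomials for the one-sided Fisher test gives 79.44% power at 72 per arm and 80.03% at 73 per arm, with an actual α of 0.0197. The stated 73 per arm and 0.0197 are reproduced. Expected occlusions: 73 × 0.19 + 73 × 0.05 = 13.87 + 3.65 ≈ 17.5.

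**2. Arm totals.** Under Binomial(146, 0.5), the probability of exactly 73:73 is 6.6%, and the central 95% range for one arm is 61 to 85. One-sided Fisher power averaged over simple randomisation is 78.8%, against 80.0% at 73:73. Part of that gap is test discreteness: 72:74 already gives 78.6–78.8%. The total split is not a material harm.

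**3. Balance within hospital.** For a hospital of size n, let q(n) be the probability that Binomial(n, 0.5) falls at 40% or less, or at 60% or more.

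| Sizes (assumed) | q by hospital | 1 − Π(1 − q) |
|---|---|---|
| 49/49/48 | 0.152, 0.152, 0.193 | 1 − 0.848 × 0.848 × 0.807 = 42% |
| 80/40/26 | 0.093, 0.268, 0.327 | 1 − 0.907 × 0.732 × 0.673 = 55% |

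A 65:35 split or worse in at least one hospital has probability 11% and 24% respectively.

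**4. How far this moves the result.** The chance arm difference due to hospital mix has SD ≈ √(4V/N), where V is the size-weighted variance of the hospital rates. With near-equal sizes:

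- 10/19/28%: V ≈ (2/3) × 0.09² = 0.0054, so SD ≈ √(4 × 0.0054/146) = 1.2 points.
- 5/19/33%: V ≈ (2/3) × 0.14² = 0.0131, so SD ≈ √(4 × 0.0131/146) = 1.9 points.

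Simulation agrees (1.2 and 1.9), and gives 1.2 and 1.8 for 80/40/26. Even 1.96 × 1.9 = 3.7 points is well below the planned 19 − 5 = 14 points.

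**5. Would the baseline rule act?** In 200,000 simulated allocations, when some hospital was 60:40 or worse, the hospital-by-arm χ² test was significant in about 12% of cases (49/49/48) or 9% (80/40/26). A significance trigger therefore misses most of these imbalances.

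**6. What the change gains.** These are two-sided simulations, so they are not comparable with the one-sided 80% above. With no device effect, simple randomisation kept the error rate: Fisher rejected in about 3.9% of trials and χ² in about 5%. With Cochran-Mantel-Haenszel used under both designs, hospital-balanced allocation added 0.5 to 1.8 points of power (for example 77.1% to 78.6%). At 8,000 runs each estimate has a standard error of √(0.77 × 0.23/8000) ≈ 0.5 point, so these are orders of magnitude. Balanced allocation with Cochran-Mantel-Haenszel, set against simple allocation with χ², gained at most about 4 points. Set against Fisher it gained up to about 11, much of which is Fisher's own conservatism. Balanced allocation analysed with unstratified Fisher lost slightly (71.6% against 72.7%).

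**The case against.** The strongest defence is that simple randomisation is a legitimate choice. Chance imbalance is already part of the sampling error that the planned tests allow for, and step 6 confirms that the error rate is kept. It is also fully unpredictable. That matters here, because unblinded ward nurses see their own ward's allocations and could partly guess the end of a block. A stratified test is, in addition, something a statistical analysis plan could settle. All of this stands, and it is why the point is an improvement and not a defect. It does not remove the point, because the allocation method is positively fixed in the article and the alternative costs almost nothing.

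A reader might infer four stronger things, none of which the document supports:

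- That nothing in the plan corrects an imbalance. The baseline rule is a listed correction; its weakness is that it depends on significance and does not name hospital.
- That hospital imbalance could mimic or mask a device effect, or that the planned tests cannot tell them apart. Under the assumed rates the shift is small against 14 points, and the tests remain valid.
- That missing 73:73 is itself harmful. It is a planning figure, and the average power cost is about 1 point.
- That these three hospitals are known to differ in flushing practice. The Background describes variation among professionals in the literature, and the Interventions section plans an educational session to standardise procedures.

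**Conclusion.** The point holds as a cheap and worthwhile refinement. Simple randomisation is fixed although a central system could stratify, no hospital adjustment is pre-specified, and the one conditional rule would seldom apply to hospital. At the assumed sizes, a split of 60:40 or worse in at least one hospital is about as likely as not (42% or 55%). The gain from changing is better hospital balance and modest precision: about 1 to 2 points of power from the allocation alone, and at most about 4 from allocation and analysis together when compared with χ².

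These sizes rest on hospital recruitment and occlusion rates that the article does not give. If the hospitals hardly differ in occlusion rate, the gain in precision is close to nil and only the balance remains.

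**What to change.** Before recruitment starts, make two changes together:

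1. In the randomisation section, replace simple randomisation with random permuted blocks stratified by hospital, keeping the 1:1 ratio and the same central online system. Vary the block sizes at random and conceal them from the sites.
2. In the analysis section, name hospital as the stratification factor and compare occlusion with a Cochran-Mantel-Haenszel test stratified by hospital, whatever the baseline comparisons show.

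Doing only the first would leave an unstratified test that is conservative under stratified allocation.

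The cost is a setting in the randomisation service and a sentence of analysis text; N stays at 146. As an illustration, blocks of 4 limit the arm difference to 2 per hospital and 3 × 2 = 6 overall, at worst 70:76. The downside is some predictability at block ends on an unblinded ward, which varied and concealed block sizes limit but do not remove.
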